## Abstract

**Background::**

Breast cancer is one of the most familiar malignant tumor all over the world in women. The main treatment for the early breast cancer is surgery accompanied by the adjuvant therapy. Nevertheless, these treatments can lead to adverse reactions including sleep disturbances, fatigue, and pain. For our research, the objective is to assess the therapeutic effect of nursing program based on WeChat for the female breast cancer.

**Methods::**

This is a randomized controlled research, and it will be carried out from November 2020 to May 2021, which was granted via the Ethics Committee of the Second Affiliated Hospital of Hainan Medical University (LW2020056). In this study, patients meeting the following criteria will be included:

And patients with

In intervention group, the patients are given multi-mode nursing program based on WeChat and routine nursing. In control group, patients are given routine nursing, involving vital signs monitoring, the education of health, the monitoring of postoperative complications, as well as postoperative drainage tube nursing. The main outcomes are the change of Functional Assessment of Cancer Therapy-Breast version 4.0 (FACT-Bv4.0) score. While the secondary result is the numerical rating scale (NRS).

**Results::**

Table 1 shows the clinical results between study group and control group.

**Conclusion::**

This paper has guided nurses to develop an evidence-based protocol to improve patient care for postoperative women with breast cancer.

**Trial registration::**

This study protocol was registered in Research Registry (researchregistry6180).

## Introduction

1

Over the past several years, the increase of incidence rate of cancer and its influence on distinct psychological, physiological, and social levels in human life make it a vital issue in this century.^[1]^ In developed countries, incidence of breast cancer ranges from 1% to 2%, with approximately 5% yearly increase in less developed countries.^[2]^ It is estimated that more than 7 million people worldwide die from the cancer. The number of novel cancer cases is projected to rise from 15 million to 20 million by 2025.^[3]^ Furthermore, breast cancer is the most familiar kind of malignant tumor in women, with more than 1 million new cases annually.^[4,5]^

Breast cancer is a kind of tissue cancer, and chiefly involving the ducts, and the inner layer of lobules or milk glands.^[6]^ The main risk factors for the cancer involve race, high levels of hormone, age, dietary iodine deficiency as well as economic status.^[7,8]^ The breast cancer affects approximately 1/8 of the female population. Most of the time, thorough tissue removal, radiotherapy, chemotherapy, and the hormone therapy are necessary.^[9–12]^ Nevertheless, these treatments can lead to adverse reactions including sleep disturbances, fatigue, and pain. Such effects can significantly worsen the life quality of patients, especially in the periods after receiving surgery accompanied by the adjuvant treatment. Some methods have been utilized for the improvement of the life quality for female breast cancer patients. Previous studies have indicated that WeChat appears to be effective in improving postoperative nursing.^[13,14]^ However, few studies reported the use of WeChat in breast cancer. Therefore, we perform this protocol to assess the therapeutic effect of nursing program based on WeChat for the female breast cancer.

## Methods

2

### Study design

2.1

It is a randomized controlled experiment to be conducted from November 2020 to May 2021. It was permitted through the Ethics Committee of the Second Affiliated Hospital of Hainan Medical University (LW2020056), and this experiment was registered with research registry (researchregistry6180).

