### Inclusion and exclusion criteria

2.2

100 patients are included in the trial. In this study, patients meeting the following criteria will be included:

(1)patients aged 18 or older,(2)stage I to III disease,(3)patients newly diagnosed with the breast cancer, and(4)patients undergoing surgery accompanied by adjuvant therapy.

And patients with

(1)mental or cognitive disorders and(2)other malignancies will be excluded.

Sequence of random numbers is generated by a computer. Sequentially numbered sealed opaque envelopes are used for the concealment of random numbers. All patients participating in our experiment are randomly assigned to the study group and the control group, each group with 50 members.

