### Intervention

2.3

In intervention group, the patients are given multi-mode nursing program based on WeChat and routine nursing, the details are as follows:

(1)Physical rehabilitation:a.Offer the personalized information: adverse reactions of the adjuvant therapy; postoperative complications; complications of an implantable venous access or the peripheral insertion of central catheter.b.Self-monitoring and prevention of recurrence after discharge.c.Drawing up and then updating the patient-oriented activity, rest, and diet plans.d.Dealing with the fatigue and lack of sleep: engaging in physical activity and relaxation exercise (such as meditation, listening to music, muscle relaxation).(2)Psychological rehabilitation:a.Conducting demand-oriented psychological counseling.b.Family (face-to-face guidance by professionals): meeting the patients’ needs; understanding their feelings; and accompanying them as much as possible.c.Peers (face to face guidance by professionals): sharing relevant experiences in coping with the negative mental state.(3)Social rehabilitation: Role transformation: Gradually accomplishing the transformation of role from the patient to social role; and fulfill their original social role.

The project team based on WeChat involves 3 researchers and 1 postgraduate student majoring in breast cancer nursing, and 1 nurse and 1 doctor from the surgical department of breast cancer. All the members take part in scheme design; 2 of the members are tasked with preparing and transmitting information; 3 members are responsible for handling issues that arise on WeChat platform. The intervention duration ranges from hospitalization to 6 months postoperatively. In control group, patients are given routine nursing, involving vital signs monitoring, the education of health, the monitoring of postoperative complications, as well as postoperative drainage tube nursing.

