### Outcomes

2.4

The main outcomes is the change of Functional Assessment of Cancer Therapy-Breast version 4.0 (FACT-Bv4.0) score.^[15]^ The evaluation includes social well-being, physical health, functional well-being, and emotional well-being, as well as the “breast cancer-specific additional concerns subscale.” While the secondary result is the numerical rating scale (NRS).

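### The stated trial dates fit a programme running to 6 months after surgery only if all 100 patients are operated on by 30 November 2020

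*Protocol article*

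**What the plan says.** Four statements in the protocol article bear on this point.

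- **Calendar.** Section 2.1 (Study design): "It is a randomized controlled experiment to be conducted from November 2020 to May 2021". The Methods paragraph of the abstract agrees: "it will be carried out from November 2020 to May 2021". Both describe when the trial takes place; neither calls the dates a recruitment period.
- **Duration per patient.** Section 2.3 (Intervention): "The intervention duration ranges from hospitalization to 6 months postoperatively".
- **Size and entry.** Section 2.2 (Inclusion and exclusion criteria): "100 patients are included in the trial", who are "randomly assigned to the study group and the control group, each group with 50 members". They are newly diagnosed and are "patients undergoing surgery accompanied by adjuvant therapy", so each patient's 6 months are counted from that patient's own operation.
- **Primary outcome.** Section 2.4 (Outcomes): "The main outcomes is the change of Functional Assessment of Cancer Therapy-Breast version 4.0 (FACT-Bv4.0) score". The sentence ties the change to no time after surgery.

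**The concern.** A trial that recruits surgical patients one after another needs its recruitment time plus the follow-up of the last patient. Here the follow-up implied by the programme takes up nearly the whole stated calendar, so little is left for recruitment.

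Two things are at stake. The first is delivery: if the trial closes in May 2021 as written, anyone in the study group operated on after November 2020 receives less than the stated 6 months. The second is the meaning of the primary outcome. The article says in its introduction and discussion that quality of life suffers particularly in the period after surgery and adjuvant treatment, so time since surgery plausibly affects the FACT-B score itself. If patients were assessed at different times since surgery, the mean change would refer to no single point in recovery.

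**Working it through.** The article states no figure for recruitment time or accrual, so there is none to reproduce. The check is date arithmetic.

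**Inputs**
- Calendar: November 2020 to May 2021 (abstract and section 2.1)
- Programme: to 6 months after surgery (section 2.3)
- Sample size: 100, as 50 per group (section 2.2)

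**Step 1. Longest possible window.** From 1 November 2020 to 31 May 2021, inclusive: 30 + 31 + 31 + 28 + 31 + 30 + 31 = 212 days.

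**Step 2. Latest surgery date.** Study end minus 6 months: 31 May 2021 minus 6 months = 30 November 2020. Surgery on 1 December would complete 6 months on 1 June, after the window closes.

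**Step 3. Entry window and required rate.** 1 to 30 November is 30 days. 100 / 30 = 3.3 patients per day; 100 / (30 / 7) = 23.3 per week. Admission, consent and randomisation must also fit within these days.

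**Step 4. Other readings of the month-only dates**

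| Start | End | Days in window | Days available for surgery |
|---|---|---|---|
| 1 Nov 2020 | 31 May 2021 | 212 | 30 |
| 1 Nov 2020 | 1 May 2021 | 182 | 1 |
| 15 Nov 2020 | 15 May 2021 | 182 | 1 |
| 30 Nov 2020 | 1 May 2021 | 153 | none |

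The first row is the most favourable to the plan and is used below.

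**Step 5. Share able to complete 6 months if recruitment runs longer.** This assumes surgery dates spread evenly from 1 November 2020 and closure on 31 May 2021. Share = 30 / (days of recruitment).

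| Recruitment | Share completing 6 months | Shortest follow-up (months of 30.44 days) |
|---|---|---|
| 1 month | 30/30 = 100% | 6.0 |
| 2 months | 30/61 = 49% | 5.0 |
| 3 months | 30/92 = 33% | 3.9 |
| 4 months | 30/120 = 25% | 3.0 |
| 5 months | 30/151 = 20% | 2.0 |
| 6 months | 30/181 = 17% | 1.0 |
| 7 months | 30/212 = 14% | 0 |

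The last row is an extreme, since it has patients entering up to the closing day.

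**Step 6. From calendar to primary outcome.** This step is conditional. If FACT-B is taken at the end of intervention or at trial close, and the trial closes in May, the follow-up behind the change score would vary between patients, from 6 months down to the figure in the last column. If it is taken at an earlier fixed time that every patient reaches, the outcome is uniform, but the 6-month programme still does not fit the calendar.

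**The case against.** **The statements are not strictly incompatible.** A reader might infer that dates, size and duration cannot all hold. The documents do not support that: a window of up to 30 days exists on the most generous reading, and the article gives neither surgical volume nor accrual rate against which to judge 3.3 patients per day. This objection stands. The plan leaves a very narrow window, and nothing in the article shows that it can be met.

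**The dates may loosely mean enrolment.** If so, the conflict disappears. But both places describe the trial as a whole, and no separate recruitment or follow-up period is stated. The text as written needs correcting even if this was the intention.

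**The effect on the primary outcome is inferred.** A reader might conclude that FACT-B will be measured at unequal or truncated follow-up. The article does not say so, and an assessment schedule may sit in a full protocol that is not shown. The missing time point is therefore not a fault in itself here; it matters only because the stated calendar would not let every patient reach the most natural time, the end of the programme.

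**Randomisation protects the comparison.** This also stands: shortened follow-up should be similar in both arms on average, so bias between arms does not necessarily follow. Balance does not, however, restore the undelivered part of the programme or give the estimate a defined time point.

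**Treatment stage.** It is tempting to contrast early patients still on adjuvant therapy with 6-month patients who have finished it. The article gives no duration for adjuvant therapy, so that contrast has no support.

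**Conclusion.** The point holds as a conflict between the stated calendar and the stated duration, given the sample size. The two fit only if all 100 patients have surgery by 30 November 2020, within at most 30 days at about 3.3 per day. This part needs no assumption beyond reading the dates as covering the whole trial, and it already uses the reading kindest to the plan.

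The size of any shortfall depends on accrual, which is not given. Under uniform accrual, 49%, 33% or 14% of patients could complete 6 months by 31 May 2021 with recruitment over 2, 3 or 7 months. These percentages illustrate the range and do not forecast this trial.

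The shortened programme for later patients follows if the calendar is kept. Mixed follow-up in the primary change follows only if FACT-B is also taken at the end of intervention or at trial close. Its consequence would then be added noise and an unclear estimand, not an established bias between arms.

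**What to change.** Reconcile the dates in the abstract and section 2.1 with the duration in section 2.3:

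- Label November 2020 to May 2021 as the recruitment period and set the study end at 6 months after the last patient's surgery. Alternatively, name a recruitment closing date and move the study end to at least 6 months after it. Keeping May 2021 as the study end would bring back the November-only window.
- In section 2.4, state one FACT-B assessment time after surgery, common to both arms, with a visit window. The end of the 6-month intervention is one example; what matters is that every patient can reach the time within the corrected calendar.

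The cost is corrected dates in the protocol, ethics file and registration, one added sentence in section 2.4, and results later than May 2021. Sample size and programme content are unaffected.

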### Inclusion and exclusion criteria

2.2

100 patients are included in the trial. In this study, patients meeting the following criteria will be included:

(1)patients aged 18 or older,(2)stage I to III disease,(3)patients newly diagnosed with the breast cancer, and(4)patients undergoing surgery accompanied by adjuvant therapy.

And patients with

(1)mental or cognitive disorders and(2)other malignancies will be excluded.

Sequence of random numbers is generated by a computer. Sequentially numbered sealed opaque envelopes are used for the concealment of random numbers. All patients participating in our experiment are randomly assigned to the study group and the control group, each group with 50 members.

### Intervention

2.3

In intervention group, the patients are given multi-mode nursing program based on WeChat and routine nursing, the details are as follows:

(1)Physical rehabilitation:a.Offer the personalized information: adverse reactions of the adjuvant therapy; postoperative complications; complications of an implantable venous access or the peripheral insertion of central catheter.b.Self-monitoring and prevention of recurrence after discharge.c.Drawing up and then updating the patient-oriented activity, rest, and diet plans.d.Dealing with the fatigue and lack of sleep: engaging in physical activity and relaxation exercise (such as meditation, listening to music, muscle relaxation).(2)Psychological rehabilitation:a.Conducting demand-oriented psychological counseling.b.Family (face-to-face guidance by professionals): meeting the patients’ needs; understanding their feelings; and accompanying them as much as possible.c.Peers (face to face guidance by professionals): sharing relevant experiences in coping with the negative mental state.(3)Social rehabilitation: Role transformation: Gradually accomplishing the transformation of role from the patient to social role; and fulfill their original social role.

The project team based on WeChat involves 3 researchers and 1 postgraduate student majoring in breast cancer nursing, and 1 nurse and 1 doctor from the surgical department of breast cancer. All the members take part in scheme design; 2 of the members are tasked with preparing and transmitting information; 3 members are responsible for handling issues that arise on WeChat platform. The intervention duration ranges from hospitalization to 6 months postoperatively. In control group, patients are given routine nursing, involving vital signs monitoring, the education of health, the monitoring of postoperative complications, as well as postoperative drainage tube nursing.

### Outcomes

2.4

The main outcomes is the change of Functional Assessment of Cancer Therapy-Breast version 4.0 (FACT-Bv4.0) score.^[15]^ The evaluation includes social well-being, physical health, functional well-being, and emotional well-being, as well as the “breast cancer-specific additional concerns subscale.” While the secondary result is the numerical rating scale (NRS).

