### Statistical analysis

2.5

Through utilizing the software of IBM SPSS Statistics for Windows, version 20, all the data can be analyzed (IBM Corp., Armonk, NY). Afterwards, all the data are described with appropriate characteristics such as mean, median, standard deviation, as well as percentage. The qualitative parameters for the groups are evaluated by *t* test. The categorical variables are determined by the *χ*^2^ tests. When *P* is less than .05, it is viewed to be significant in statistics.

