## Results

3

Table 1 shows the clinical results between study group and control group.

**Table 1 T1:** Clinical results between study group and control group.

Variables	Study group (n = 50)	Control group (n = 50)	*P*
Physical well-being			
Social well-being			
Emotional well-being			
Functional well-being			
Breast cancer-specific subscale for additional concerns			
Numerical rating scale			
Postoperative complications			

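### The plan does not say which FACT-B score is primary, and its results table lists only the five subscales, each with its own unadjusted P

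*Protocol article*

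**What the plan says.** - **Section 2.4 (Outcomes):** "The main outcomes is the change of Functional Assessment of Cancer Therapy-Breast version 4.0 (FACT-Bv4.0) score". The next sentence describes the content of the instrument: "The evaluation includes social well-being, physical health, functional well-being, and emotional well-being, as well as the" breast-specific concerns subscale. The section does not use the word total, and it sets no baseline and no assessment time. The NRS is named as the secondary outcome.
- **Abstract, Methods:** the same outcome with a plural verb: "The main outcomes are the change of Functional Assessment of Cancer Therapy-Breast version 4.0 (FACT-Bv4.0) score".
- **Section 3, Table 1:** an empty shell with seven rows: physical, social, emotional and functional well-being, "Breast cancer-specific subscale for additional concerns", the NRS and postoperative complications. Its columns are study group (n = 50), control group (n = 50) and P. There is no FACT-B score row, and no row or column is labelled baseline, follow-up or change.
- **Section 2.5 (Statistical analysis):** when P "is less than .05, it is viewed to be significant in statistics". The section does not say which score decides the trial.

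**The concern.** The outcome statement and the table shell do not fit together. A reader of Section 2.4 expects a result for the change in a FACT-B score. A reader of Table 1 finds five subscale comparisons, each with its own P, and no such result.

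Two things are at stake. First, the question posed in Section 2.4 may have no planned place in the results. Second, because no score is named as decisive and every P is judged at .05, the choice of which FACT-B result counts as the main finding can be made after the data are seen. A claim on the main outcome could then rest on any one of five subscales, and the 5% error rate that a reader attaches to a primary result would not apply.

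**Working it through.** **Setting the sections side by side.** Section 2.4 can be read in two ways.

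1. *The primary is one score.* The singular score supports this. Table 1 then has no row for the primary outcome, and its five FACT-B rows are component results.
2. *The primary is the five domains.* The plural outcomes, followed at once by a list of five domains, supports this. The rows of Table 1 then match Section 2.4, but there are five primary tests at .05 each, with no rule for how many must succeed.

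Neither reading gives a primary analysis that is both listed in the table and controlled at 5%.

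**Inputs for the second reading**
- Number of subscales: 5 (Section 2.4 and Table 1).
- Threshold per test: .05 (Section 2.5). Sidedness is not stated, so two-sided is assumed.
- Patients per arm: 50 (Section 2.2).
- Test: *t* test for each subscale. Section 2.5 says "The qualitative parameters for the groups are evaluated by" *t* test, and I take this to cover the continuous scores.
- Correlation between subscales: not in the document, so assumed, with a range shown.

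The article gives no family-wise error rate to reproduce. Its only stated figure for error is the .05 per test.

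**Independent subscales, no true effect**
- At least one P below .05 in either direction: 1 − 0.95^5 = 1 − 0.774 = 0.226, or 22.6%.
- At least one P below .05 in favour of the intervention: 1 − 0.975^5 = 1 − 0.881 = 0.119, or 11.9%.

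**Correlated subscales.** Simulation of five equally correlated normal scores, 50 per arm, two-sided *t* tests at .05, 40,000 runs per setting:

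| Assumed correlation | Any false positive | Any false positive favouring the intervention |
|---|---|---|
| 0 | 22.1% | 11.7% |
| 0.3 | 20.7% | 10.5% |
| 0.5 | 18.7% | 9.3% |
| 0.7 | 15.1% | 7.5% |
| 0.8 | 12.8% | 6.5% |

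The row for zero correlation agrees with the exact values to about half a percentage point. A single two-sided test has 5%, of which 2.5% favours the intervention.

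**What each repair does.** One pre-named test at .05 has an error rate of 5%. If the five subscales were kept as primary with Bonferroni, each would be tested at .05/5 = .01, and the family-wise error under independence would be 1 − 0.99^5 = 0.049. The standardised difference detectable with 80% power at 50 per arm would move as follows:
- at .05: (1.960 + 0.842) × √(2/50) = 0.56
- at .01: (2.576 + 0.842) × √(2/50) = 0.68

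**The case against.** The strongest reply is that this is a condensed article with an empty table, and that a statistical analysis plan may exist. Much of that stands:

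- A reader might infer that the primary result will never be produced. The document does not show this. One column per arm could hold mean changes, and a total could be reported outside Table 1. It shows only that the published shell does not list such a result.
- A reader might infer that five co-equal primary tests are established. They are one of two readings. Nowhere are the subscales called primary, and nowhere is any one of them said to decide the trial.
- A reader might infer that a false-positive main outcome is likely. At about 13% to 23% it is inflated but well below even odds. For a claim that the intervention works, only favourable results count, and there the figure is about 6.5% to 11.9%. Independence is the upper end of these ranges, and subscales of one questionnaire are probably correlated.
- A reader might extend the sum to all seven rows, 1 − 0.95^7 = 30.2%. That does not bear on the primary claim: the NRS is secondary, and postoperative complications are not listed as an outcome in Section 2.4.
- How secondary subscales are adjusted and how tables are laid out in detail are normally matters for the analysis plan, so their absence is not a fault here.

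What the reply does not answer is the identity of the primary score. An outside document can fill a silence, but here the authors published both an outcome statement and a row-by-row table, and the two do not identify the same result. An analysis plan that added a total-score row would have to depart from the published shell.

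**Conclusion.** The concern holds as a defect in how the primary outcome is identified. Section 2.4 does not say which FACT-B score is primary, and the table shell and the .05 rule leave either an unlisted primary outcome or five unadjusted primary tests. Under the second reading the false-positive rate is about 2.5 to 4.5 times the nominal 5% (12.8/5 = 2.6 at a correlation of 0.8, and 22.6/5 = 4.5 under independence). These figures rest on two-sided tests, no true effect on any subscale, and assumed equal correlations that the document does not supply. Under the first reading the multiplicity figures do not apply to the primary test, and the defect is that the planned table omits it. In both cases the deciding result should be fixed before any outcome data are seen.

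**What to change.** In Section 2.4 and the Abstract, name the change in FACT-B total score from baseline to one stated time point as the single primary outcome, and in Section 2.5 say that it is tested once at two-sided .05. Add that row, as change, to Table 1. Label the five subscales secondary, and state that no success claim will rest on a subscale alone.

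The sponsor must state the time point. Section 2.3 gives 6 months only as the length of the intervention, not as an assessment time. Section 2.1 runs the study from November 2020 to May 2021, so a 6-month assessment inside those dates would be possible only for patients operated on near the start.

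The cost is a few sentences and one table row. No extra data are needed if FACT-B is already collected in full at baseline and at the chosen time, which the article does not confirm. The downside is that a result on a single subscale can no longer be called a primary success. Keeping all five subscales as primary under Bonferroni would also control the error, but it raises the detectable standardised difference at 50 per arm from 0.56 to 0.68.
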